##### The intervention group (the O2O-PEP mini-app)

The O2O-PEP mini-app is the primary user-oriented platform for the intervention group. Following randomization, intervention group participants are directed to the gamification-based PEP education package, with a link to make online bookings anonymously available on the screen whenever participants want to click during the gamification procedure. After successful online booking, clients present their PEP prescription requisition e-ticket to the clinical doctor in the study-selected hospital, the clinical doctor will start the PEP regimen according to the Chinese national guideline, and the nurse in the same department will conduct essential PEP counseling when requested by participants. Participants will not be permitted to share the study advertisement with others. To restrict access to the min-app to intervention group participants only, those randomized into the intervention group will be provided a single-use verification code which will be entered to gain access to the intervention. Participants will have unlimited access to the mini-app after randomization until the end of the study.

##### The control group (routine PEP-related care)

Participants in the control group would not be directed to the O2O-PEP mini-app after randomization, but will receive HIV- and PEP-related services following the current practices in health care services, including electronic HIV prevention materials, referrals to local PEP services, and a standard procedure to access PEP through the study hospital.

##### Follow-ups

Follow-ups will be conducted at 1, 3, and 6- months after randomization. In each follow-up, participants are invited to complete a survey relating to social support, HIV health literacy, HIV risk perception, sexual and HIV risk behaviors, mental health, and PEP uptake. Each participant will be compensated 50 RMB (the currency of China), or ~$ 8. After 1 week, participants who do not respond to the investigation will be sent a reminder offering them one additional week for completion.

##### Sample size

Our previous study found that ~5% of MSM self-reported using PEP before the survey (36). A sample of ~400 participants (200 per group) would achieve 90% power to detect a moderate effect corresponding to a difference of at least 9% points (equivalent to a relative risk of 2.8 assuming a 5% prevalence of PEP usage in the control group) in PEP uptake between the intervention and control groups using a two-sided test at a 5% significance level and assuming a 10% attribution rate after 6 months. According to Cocks et al. (37) the sample size of a pilot trial should be at least 9% of that of the main planned trial. Hence, we plan to recruit 50 participants, 25 per group, to assess preliminary evidence for the further main study.

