**Laboratory testing**					
HIV Ag/Ab testing	HIV-1/2	√	√	√	√
Syphilis	Syphilis serology	√	√		√
Gonorrhea/ Chlamydia	first-catch urine, oral, urethral, and rectal mucosal secretions	√	√		
HBV	HBsAg, anti-HBs, anti-HBc	√			√
HCV	HCV antibody test	√			√
Serum creatinine	Kidney function test	√	√		
ALT, AST	Liver function test	√	√		

The primary efficacy outcome is PEP initiation. PEP initiation data will be collected through the clinical records in the study hospitals, which is a binary variable (1 = PEP initiation during the study period, otherwise 0). The acceptability outcome will be measured by the System Usability Scale (SUS) (30). For feasibility, we will assess the cumulative exposure time to the mini-app, as well as time spent on specific components of the mini-app, which will be automatically collected by participant application log files.

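### The 5% control rate is past self-reported PEP use with no stated look-back, not 6-month recorded initiation, so the power at 400 and the basis of the 9% pilot rule are not established for the trial's own endpoint

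*Protocol article*

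**What the plan says.** All planning figures are in the Sample size section of the protocol article. The control rate comes from the team's own survey: "Our previous study found that ~5% of MSM self-reported using PEP before the survey". It then enters the calculation as the control-arm value: "assuming a 5% prevalence of PEP usage in the control group". The target is "a difference of at least 9% points (equivalent to a relative risk of 2.8" at that rate). The claim is that about 400 participants, 200 per group, "would achieve 90% power to detect a moderate effect", "using a two-sided test at a 5% significance level", "assuming a 10% attribution rate after 6 months" (read here as attrition). The section then cites a rule that a pilot should have at least 9% of the main trial's size, and from this sets the pilot at 50, 25 per group.

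The endpoint is defined under Outcomes and covariates of the study. It comes from the study hospitals' clinical records and is coded "1 = PEP initiation during the study period, otherwise 0". The Statistical analysis plan section counts any initiation over follow-up and compares the groups by an unadjusted risk ratio. The Follow-ups section places the last visit at 6 months.

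**The concern.** The planning rate and the endpoint differ in three ways:

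- **Kind:** having used PEP in the past, against starting PEP anew.
- **Window:** none stated, against 6 months.
- **Source:** self-report, against records of two hospitals.

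The article neither converts one into the other nor argues that they are equal.

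The 5% does two jobs. It sets the variance and event count behind the 400, and it makes the two statements of the effect agree. At any other control rate, 9 points and RR 2.8 are different targets and the main trial's size depends on which is meant. The pilot's 50 is justified only as a fraction of that size, so the justification inherits the uncertainty. The pilot is meant to inform the main study. If 5% is carried forward unexamined, the main trial could be badly sized for its own outcome.

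**Working it through.** **Inputs (Sample size section):** control 5%, intervention 14% (5% + 9 points; 14/5 = 2.8), two-sided 5%, 90% power, 10% loss, 1:1 allocation, 400 in total, pilot at least 9% of the main trial.

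**Formula.** Pooled two-proportion test, with p̄ = (p₁ + p₂)/2:

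n per arm = [1.960·√(2p̄(1−p̄)) + 1.282·√(p₁(1−p₁) + p₂(1−p₂))]² / (p₂ − p₁)²

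Total = 2 × (n/0.9), rounded up per arm.

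**Step 1: the plan's own figure.** With p̄ = 0.095, the square roots are 0.4147 and 0.4098:

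- n = (0.8127 + 0.5251)²/0.0081 = 221 per arm.
- 221/0.9 gives 246 per arm, **492** in total, against the stated 400.
- With 200 × 0.9 = 180 evaluable per arm, power = Φ[(0.09·√180 − 0.8127)/0.4098] = Φ(0.963) = **83%**. With all 200 per arm it is 87%.
- Other two-sided formulas also miss 200 per arm after loss: unpooled variance about 242, arcsine 234, continuity correction 270, log-RR 277.
- A one-sided 5% test gives 180 per arm, or 200 after loss. That matches the stated number but not the stated test.

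This shortfall exists even if 5% is right, so it is separate from the mismatch.

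**Step 2: vary the control rate.** The article gives no 6-month initiation rate under routine care, so the 1–5% range is an assumption. Power is for 180 evaluable per arm; the 9% figure is rounded up because the rule is a minimum.

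| Control rate | RR 2.8 held: total | power | 9% | 9 points held: total | power | 9% | RR implied by 9 points |
|---|---|---|---|---|---|---|---|
| 5% | 492 | 83% | 45 | 492 | 83% | 45 | 2.8 |
| 4% | 630 | 73% | 57 | 446 | 87% | 41 | 3.25 |
| 3% | 858 | 60% | 78 | 396 | 90% | 36 | 4.0 |
| 2% | 1,314 | 43% | 119 | 348 | 94% | 32 | 5.5 |
| 1% | 2,684 | 24% | 242 | 296 | 97% | 27 | 10 |

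**Step 3: the 9% rule.** Fifty is at least 9% of a main trial of up to 50/0.09 = 555. With RR 2.8 held, a 4.5% control rate gives 249 per arm and a total of 554, so about 4.5% is the lowest rate at which 50 meets the rule. With 9 points held, 50 meets it at every rate in the table.

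**Step 4: can the pilot supply the rate?** At 5% versus 14%, the expected events are 25 × 0.05 + 25 × 0.14 = 4.75, about 5. At 2% versus 5.6% they are 0.5 + 1.4 = 1.9, about 2. Exact 95% intervals are 3.3–21.8% for 5/50 and 0.5–13.7% for 2/50. They overlap across most of the range in question, and a pooled rate gives a control rate only if the treatment effect is assumed.

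**The case against.** **The stronger reading.** A reader might infer that the main trial must become much larger and that the pilot of 50 fails its own 9% rule. The documents do not support this. The target is stated first as 9 percentage points, with RR 2.8 in brackets as its equivalent. If 9 points is the target, a lower control rate makes the main trial smaller and 50 always suffices. This part of the objection stands. The other side is that the analysis uses a risk ratio, and that 9 points at a 1–2% control rate means an RR of 10 to 5.5, which sits badly with an effect described as moderate. The article does not settle which target is meant.

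**Direction of the error.** A reader might also take the 5% as use at any time, and so as certainly too high for 6 months. Lifetime use is a natural reading of use before a survey, but the look-back is not stated. Referral to other PEP services could send initiations outside the two hospitals' records and lower the rate. Against that, controls get prevention materials and a standard access route at the study hospital, and the Discussion mentions partial subsidy of drug and test costs without naming an arm. Lower than 5% is plausible but not shown.

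**Low stakes.** The trial is a pilot for feasibility, acceptability and preliminary evidence, and the Discussion admits that the sample is small. This limits the harm to the pilot itself. It does not remove the gap in the main-trial calculation from which the pilot's size is derived.

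**Conclusion.** The concern holds as a gap in justification. A self-reported prevalence with no stated look-back is used as the control rate for recorded 6-month initiation, and nothing in the article equates them. The power at 400 and the basis of the 9% rule are therefore not established for the trial's endpoint. No single corrected number exists: over an assumed 1–5%, the main-trial total runs from 492 up to 2,684 with RR 2.8 held and from 492 down to 296 with 9 points held. These figures rest on the pooled two-proportion formula, 90% power and 10% loss.

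Neither a too-small pilot nor the direction of the error is shown. The shortfall at the stated 5% (83% power at 400, 492 needed for 90%) is a separate arithmetic error and should not be put down to the mismatch.

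**What to change.** In the Sample size section:

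1. State the look-back period of the surveyed 5%.
2. Replace the single value with an assumed range for 6-month initiation under routine care as recorded in the study hospitals, for example 1–5%.
3. Say whether 9 points or RR 2.8 is the target, and drop the equivalence except at 5%.
4. Report main-trial total, power and the 9% figure for each rate. If RR 2.8 is the target, say that 50 meets the 9% rule only at about 4.5% or above; if 9 points is the target, say that it meets the rule throughout the range.
5. Correct the 5% versus 14% calculation: 492 for 90% power, or about 83% power at 400.
6. Say that the main trial's control rate will come mainly from 6-month PEP counts at the two hospitals or other external data, not from the pilot's pooled rate.

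The cost is protocol text and less favourable stated figures. Pilot enrolment does not change.

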##### Statistical analysis plan

All statistical analyses will be conducted using SAS software (version 9.4, SAS Institute, Inc. USA), with a two-sided *p*-value of <0.05 considered statistically significant. The primary analysis will be performed by intention-to-treat analysis. Descriptive statistical analysis will be first carried out to report baseline demographics, outcome variables, and other covariates at different follow-up time points, and then compared with Chi-square/Fisher exact probability tests (for categorical variables) or *t*-test/Mann Whitney U test (for continuous variables) between those who finish follow-ups and those who do not and between the mini-app group and the control group.

The preliminary efficacy of the min-app intervention to increase PEP initiation (any PEP initiation over follow-ups) will be evaluated using an unadjusted risk ratio. As for model acceptability, point estimates for a SUS score of ≥50 will be considered the minimum criteria for acceptability. Descriptive analysis will be used to evaluate model usability, including cumulative time to the mini-app, and time spent on specific components of the mini-app. Multiple imputations will replace missing data, and a sensitivity analysis will be performed to compare the multiple imputation analysis with the full case analysis.

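### The stated 90% power for about 400 participants does not follow from the plan's inputs: the two-sided 5% test gives about 83%, and 90% matches a one-sided test

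*Protocol article*

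**What the plan says.** The Sample size section sizes a future main trial and then derives the pilot size from it. On the main trial it states: "A sample of ~400 participants (200 per group) would achieve 90% power to detect a moderate effect". The effect is "a difference of at least 9% points (equivalent to a relative risk of 2.8", "assuming a 5% prevalence of PEP usage in the control group", so the comparison is 5% against 14%. The test and the loss are given as "using a two-sided test at a 5% significance level and assuming a 10% attribution rate after 6 months"; the word for the loss is evidently meant to be attrition.

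The Statistical analysis plan section also sets a two-sided criterion: "with a two-sided *p*-value of <0.05 considered statistically significant". No one-sided test appears anywhere in the article. The Randomization section gives 1:1 allocation.

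The pilot size of 50 (25 per group) is then justified by a cited rule that a pilot should have at least 9% of the main trial's participants.

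**The concern.** One sentence gives every input to the power calculation together with its result, so the result can be checked directly. It does not follow from the inputs. The error runs in the favourable direction: the trial looks better powered than it is.

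Two things depend on the figure. It is the article's only published size for the main trial, so a team that carries it forward would plan with a false-negative risk of about 17% at the target effect while believing it to be 10%. It is also the base to which the 9% rule for the pilot is applied.

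**Working it through.** **Inputs** (Sample size section, except allocation)

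- Control 5%, intervention 14% (5% + 9 points; 0.05 × 2.8 = 0.14), difference 0.09
- Two-sided alpha of 5%
- 200 per group, 10% loss: 200 × 0.9 = 180 evaluable per group
- Allocation 1:1 (Randomization section)

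**Formula.** For the pooled-variance two-proportion z-test, with mean proportion (0.05 + 0.14)/2 = 0.095:

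- Null term: A = √(2 × 0.095 × 0.905) = √0.17195 = 0.4147
- Alternative term: B = √(0.05 × 0.95 + 0.14 × 0.86) = √0.1679 = 0.4098
- n per group = (z_α·A + z_β·B)² / 0.09²
- Power = Φ[(0.09 − z_α·A/√n) / (B/√n)]

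**Can the plan's own figure be reproduced?** Only with a one-sided 5% critical value (1.645) when all the other stated inputs are used:

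- n = (1.645 × 0.4147 + 1.2816 × 0.4098)² / 0.0081 = (0.6821 + 0.5251)² / 0.0081 = 179.9, so 180 evaluable per group
- 180 / 0.9 = 200 per group, 400 in total
- Power at 180 per group: Φ(1.282) = 90.0%

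**With the stated two-sided test** (1.960), 180 per group:

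- A/√180 = 0.03091 and B/√180 = 0.03054
- (0.09 − 1.960 × 0.03091) / 0.03054 = 0.963
- Power = Φ(0.963) = 83.2%

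**Size needed for 90% two-sided:**

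- n = (1.960 × 0.4147 + 1.2816 × 0.4098)² / 0.0081 = (0.8127 + 0.5251)² / 0.0081 = 221 evaluable per group
- 221 / 0.9 = 245.6, so 246 per group and 492 in total

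**Other two-sided methods**

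| Method | 180 per group | 200 per group (no loss) |
|---|---|---|
| Pooled z | 83.2% | 86.9% |
| Unpooled z | 83.8% | 87.4% |
| Arcsine | 85.0% | 88.5% |
| Continuity-corrected z | 78.3% | 82.9% |
| Wald, log risk ratio | 78.7% | 82.7% |
| Wald, log odds ratio | 79.8% | 83.8% |
| Fisher's exact test | 79.8% | 84.6% |
| Pearson chi-square, exact enumeration | 84.7% | 88.0% |
| Likelihood-ratio test, exact enumeration | 85.5% | 89.0% |

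No entry in either column reaches 90%. The required total also depends on the method: about 468 with arcsine and 540 with the continuity correction, around the 492 of the pooled formula.

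**Detectable effect.** With 180 per group and the pooled two-sided formula, 90% power is reached at about 15.2% in the intervention group. That is a difference of about 10.2 points, not 9.

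**Effect on the pilot.** The 9% rule gives 0.09 × 400 = 36, 0.09 × 492 = 44.3 and 0.09 × 540 = 48.6. All are below the planned 50.

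**The case against.** The best defence is that 180 may be the wrong denominator. According to the section on outcomes and covariates, PEP initiation is taken from study-hospital records and coded 0 when no initiation is recorded. The analysis is by intention to treat, with multiple imputation. A participant who stops answering surveys can therefore still contribute a primary outcome. With 200 analysed per group the pooled power is 86.9%, and the most favourable methods give 88% to 89%. This narrows the gap but does not close it. It also sets aside a loss that the plan's sentence names as an assumption of the calculation.

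The inputs are approximate. With 4.5% against 13.5%, pooled power is 85.0% at 180 per group and 88.5% at 200. Rounding of that order does not rescue the claim. A control rate as low as 3% with the 9-point difference would give 90.3% at 180 per group, but that is neither the stated 5% nor the stated relative risk of 2.8.

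The one-sided explanation is an inference. The numerical match is exact, but the article does not show its calculation, and 400 is a round number. This caution is fair. The finding does not need the explanation, because the two-sided claim fails whatever its origin.

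Finally, the trial described here is a pilot of 50, and the main trial could be re-sized later. It is true that nothing in the pilot's conduct changes. That limits the consequence but does not make the published statement correct.

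**Conclusion.** The stated power is wrong for the test described. On the plan's own inputs, two-sided power is about 83% by the pooled formula (78% to 86% across the methods tried), 7 points below the claim. If no participant is lost to the primary analysis, it is about 87% by the pooled formula and at most 89%. For 90% power the pooled formula requires about 492 participants, 92 more than stated.

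This rests on 5% against 14%, 1:1 allocation, a two-sided 5% test and a 10% loss that reduces the analysed number. A one-sided critical value is the probable source of the error, since with the other stated inputs it reproduces both the 400 and the 90%. The harm falls on the main-trial figure and on the stated basis for the pilot size. The pilot of 50 still satisfies the 9% rule.

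**What to change.** Correct the sentence in the Sample size section in one of two ways:

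- Keep the size and restate the power: 400 participants (200 per group, 180 evaluable after 10% loss) give about 83% power for 5% against 14% with a two-sided 5% test.
- Keep the power and restate the size: about 492 participants (246 per group, 221 evaluable) give 90% power under the same assumptions.

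Name the formula used, since the figures shift by a few points between methods. Relabelling the test as one-sided is not a sound repair, because it would contradict the two-sided criterion in the Statistical analysis plan section. Replace the word attribution with attrition in the same sentence.

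The cost is one sentence of text and a less favourable published figure. The pilot size, its conduct and its analysis do not change.

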##### Outcomes and covariates of the study

Primary and secondary outcomes, covariates, and specific survey time points for each variable in the pilot RCT are shown in Table 1.

**Table 1 T1:** Data collection and survey time points.

**Variables**	**Description/scale**	**Follow-ups (months)**			
		**Baseline**	**1**	**3**	**6**
**Primary outcomes**					
Acceptability	System usability scale (30)		√		√
Feasibility	Exposure time to the mini-app		√		√
PEP initiation	PEP initiation during study time	√	√	√	√
**Secondary outcomes**					
PEP knowledge	PEP Knowledge Scale (38)	√	√	√	√
Depression	PHQ-9 (39)	√	√	√	√
Anxiety	The Zung Self-rating anxiety scale (40)	√	√	√	√
Levesque model constructs	PEP awareness, intention to use PEP, get PEP whenever you want, PEP affordability, PEP engagement	√	√	√	√
**Covariates**					
Demographics	Age, gender, marital status, local households, personal monthly income, ethnicity, education, insurance status, employment, and sexual orientation	√			
Social support	Whether received help from any of 10 sources of social support	√	√	√	√
HIV health literacy	An eight-item index (41)	√	√	√	√
HIV infection risk perception	PHRS (42)	√	√	√	√
Sexual behaviors	Unprotected anal intercourse	√	√	√	√
MSM related stigma	The homosexual stigma scale (43)	√	√	√	√
**Laboratory testing**					
HIV Ag/Ab testing	HIV-1/2	√	√	√	√
Syphilis	Syphilis serology	√	√		√
Gonorrhea/ Chlamydia	first-catch urine, oral, urethral, and rectal mucosal secretions	√	√		
HBV	HBsAg, anti-HBs, anti-HBc	√			√
HCV	HCV antibody test	√			√
Serum creatinine	Kidney function test	√	√		
ALT, AST	Liver function test	√	√		

The primary efficacy outcome is PEP initiation. PEP initiation data will be collected through the clinical records in the study hospitals, which is a binary variable (1 = PEP initiation during the study period, otherwise 0). The acceptability outcome will be measured by the System Usability Scale (SUS) (30). For feasibility, we will assess the cumulative exposure time to the mini-app, as well as time spent on specific components of the mini-app, which will be automatically collected by participant application log files.

Secondary outcomes include (1) PEP knowledge, evaluated with an 11-item scale developed by Li et al. (39) for Chinese MSM, and the Cronbach's Alpha was 0.997 (38). (2) Depression. The Patient Health Questionnaire (PHQ-9) will be used to measure the severity of depression symptoms, which scores each item as “0” (not at all) to “3” (nearly every day). The Chinese version of PHQ-9 has been previously well-validated in people living with HIV (44). (3) Anxiety. It will be assessed by the Chinese version of the Zung Self-Rating Anxiety Scale (SAS) (40). The SAS comprises 20 items, and each item was scored on a 4-point rating, increasing scores suggested an increasing severity of anxiety symptoms. Previous studies have confirmed the reliability and validity of the SAS (Cronbach's alpha = 0.85) in the Chinese population (45, 46). (4) Finally, we will assess the Levesque model constructs including the ability to perceive, ability to seek, ability to reach, ability to pay, and ability to engage. The ability to perceive will be assessed by PEP awareness, by asking participants to report whether they have heard of PEP, with a response of “Yes” or “No.” The ability to seek will be assessed by the intention to use PEP, with the question “how likely are you to use PEP when you are at risk in the next 6 months?” with a 6-point Likert response from 1 = very unlikely to 6 = extremely likely. The ability to reach will be assessed by the question “Can you get PEP when you want to use it?” with a response of “Yes” or “No.” The ability to pay will be asked “Are you able to afford PEP when you have to pay for it out of your pocket?” with a response of “Yes” or “No.” The ability to engage will be assessed by the question “Are you able to comply with PEP usage rules?” with a response of “Yes” or “No.”

Covariate variables include demographics, social support, HIV health literacy, HIV infection risk perception, sexual behaviors, and MSM-related stigma. As for social support, participants will report on whether they receive help from any of ten sources with a 5-point rating (1 = extremely harmful to 5 = extremely helpful): primary and other sexual partners; friends; siblings; parents; medical, religious, mental health, and social service professionals; and community organizations (47). HIV health literacy will be measured by an index of eight items relating to various HIV prevention and treatment practices, responses for each item are coded as correct or incorrect, and all the corrected responses are summed to determine the total score (41). The HIV health literacy index has been used for HIV-negative MSM and is positively associated with PrEP awareness (41). HIV infection risk perception will be evaluated by the 8-item Perceived Risk of HIV infection Scale (PRHS) (42). The PRHS demonstrated good reliability and concurrent criterion-related validity, with Cronbach's coefficient of 0.79 in a Chinese college student study (48). MSM-related stigma will be assessed with the Neilands' homosexual stigma scale (43), consisting of perceived stigma and enacted stigma. This scale consists of 10 items, each scoring from “0 = never” to “3 = many times.” The scale has been translated into Chinese and the Cronbach's alpha value was 0.76 (49).

To identify potential conditions that would affect PEP usage, laboratory testing will be conducted following the national guideline. These include free and voluntary HIV rapid testing (HIV-1/antibody test), HBV test (hepatitis B surface antigen [HBsAg], hepatitis B surface antibody [anti-HBs], and hepatitis B core antibody [anti-HBc]), HCV antibody test, blood Syphilis test, Nucleic Acid Amplification Test for Gonorrhea and Chlamydia (by testing first-catch urine, oral, urethral and rectal mucosal secretions), serum creatinine, and liver function test (Alanine transaminase, Aspartate transaminase).

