### Pilot randomized controlled trial

#### Study design and participants

The purpose of the pilot study is to assess the feasibility, acceptability, and preliminary evidence of the efficacy of the O2O-PEP model in increasing PEP uptake among MSM through a pilot two-arm stratified RCT comparing the O2O-PEP group with the standard care group (Figure 3). Participants will be recruited via online social media and offline CBOs. MSM are eligible to participate in our pilot study if they (1) are 18 years or older, (2) are assigned male at birth, (3) ever had anal intercourse with a man, 3) have HIV-uninfected by a laboratory rapid antibody test, (4) are going to reside in Jiangsu province and Qingdao city in the following 6 months after recruitment, (5) own a smartphone with Android-based operating system, (6) can access the WeChat app during the study period, and (7) are able and willing to provide electronic informed consent. Exclusion criteria include (1) self-reporting concomitant use of HIV PrEP at study entry, (2) creatinine clearance <30 ml/min, (3) known co-infection with chronic hepatitis B at enrollment, (4) participating in another research intervention related to PEP, (5) mental health disorders that may compromise adherence or safety, such as memory loss, cognition impairment, or communication disorders (assessed by an experienced clinical psychologist who is not involved in the study), and (6) presence of acute HIV infection symptoms [assessed by the Amsterdam score (31)].

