#### Study settings

A convenience sample will be recruited in Jiangsu and Qingdao, China, via two local MSM-related CBOs. The two CBOs are run by non-medical community staff trained to perform rapid HIV testing and consultation, PEP and PrEP counseling, and psychological support for HIV-negative and positive clients. Both CBOs have rich experience in HIV research and management. Offline PEP prescription will be conducted at Suzhou Fifth People's Hospital (Jiangsu) and Qingdao Sixth People's Hospital (Qingdao, China), both of which are among the designated PEP treatment hospitals under the national PEP uptake guideline (32).

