## Ethics statement

This study was approved by the medical institutional review board (IRB) of Binzhou Medical University (IRB No. 2021-007). All participants will sign an electronic informed consent form before enrolling in the study, which will also authorize access to their clinical records in the study hospitals. Each participant will be compensated 50 RMB each for completion of the baseline, 1, 3, and 6-month follow-ups. If the intervention proves to be effective, access to the invention is guaranteed for all high-risk MSMs even after the study has been concluded. We would also share the implementation challenges and successes in future research by reporting on international conferences and peer-reviewed articles.

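### The primary efficacy outcome sees only PEP recorded at the study hospitals, so initiations elsewhere score 0 and may be missed more often in the control arm

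*Protocol article*

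**What the plan says.** Only the protocol article is available.

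- **Outcome source and coding** (Outcomes and covariates of the study, text below Table 1): "PEP initiation data will be collected through the clinical records in the study hospitals, which is a binary variable", coded "1 = PEP initiation during the study period, otherwise 0".
- **Record access** (Ethics statement): consent is the document "which will also authorize access to their clinical records in the study hospitals". No other provider is mentioned.
- **Other providers** (Study settings): there are two study hospitals, "both of which are among the designated PEP treatment hospitals under the national PEP uptake guideline". They are thus two of a larger set.
- **Intervention route** (The intervention group): after booking, "clients present their PEP prescription requisition e-ticket to the clinical doctor in the study-selected hospital".
- **Control route** (The control group): "referrals to local PEP services, and a standard procedure to access PEP through the study hospital".
- **Self-report** (Follow-ups): surveys of all participants at 1, 3 and 6 months include "sexual and HIV risk behaviors, mental health, and PEP uptake". Table 1 lists PEP initiation at baseline and at the same three visits.
- **Analysis** (Statistical analysis plan section): an unadjusted risk ratio for any initiation across follow-up, with no limit to particular hospitals.
- **Planning rate** (Sample size): about 5% in controls, taken from self-reported use in an earlier study. The article mentions no restriction by provider.

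**The concern.** The outcome is meant to show whether a participant started PEP. As defined, it shows whether a participant started PEP in one of two hospitals. The intervention includes a booking system that leads to those hospitals. The control condition names that route and a second one.

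If the mini-app only moved users from other clinics to a study hospital, the records would show more initiations in the intervention arm although no more people had started PEP. Such an error depends on the share of initiations captured in each arm, so a larger sample would not remove it. The pilot is meant to inform a trial of about 400, and the definition would be carried forward with it.

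The article is also not consistent with itself. The analysis section speaks of any initiation, the 5% planning rate is self-reported, and the outcome section names hospital records as the source.

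**Working it through.** **1. The plan's own figure.** Control 5%, difference 9 percentage points: intervention rate = 5% + 9% = 14%, and 14/5 = 2.8. The stated relative risk reproduces. It assumes that initiations are fully counted, or equally counted, in both arms.

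**2. How capture enters.** Let c be the share of an arm's initiations that take place at the study hospitals. Then:

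observed rate = true rate × c

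observed RR = true RR × c(O2O-PEP) / c(control)

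The documents give neither share. Every share below is an assumption.

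**3. Results for a range of shares.**

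| c(O2O-PEP) | c(control) | Ratio | Observed RR if true RR = 1.00 | Observed RR if true RR = 2.80 |
|---|---|---|---|---|
| 95% | 95% | 0.95/0.95 | 1.00 | 2.80 |
| 95% | 90% | 0.95/0.90 | 1.06 | 2.96 |
| 95% | 70% | 0.95/0.70 | 1.36 | 3.80 |
| 95% | 50% | 0.95/0.50 | 1.90 | 5.32 |
| 90% | 100% | 0.90/1.00 | 0.90 | 2.52 |

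The first row shows that equal under-counting leaves the risk ratio unbiased. The last row shows that the bias would reverse if more intervention initiations were missed.

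**4. Consequence at main-trial size.** Take 200 per arm less 10% dropout = 180 per arm, equal true uptake of 5%, and full capture in the intervention arm (assumed). The chance of a significant result favouring O2O-PEP is Φ[(d − 1.96·SE₀)/SE₁], where d is the observed difference, SE₀ the pooled and SE₁ the unpooled standard error.

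- Control capture 75%: observed 5% vs 3.75%, d = 0.0125; chance about 8%.
- Control capture 50%: observed 5% vs 2.5%, d = 0.025; chance about 24%.

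The nominal value in that tail is 2.5%.

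**5. Consequence in the pilot.** At a true 5%, 25 controls yield 25 × 0.05 = 1.25 expected initiations. The chance of none is 0.95²⁵ = 28%. At an assumed 50% capture the rate is 2.5% and the chance is 0.975²⁵ = 53%. With no control event the planned risk ratio is undefined.

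**6. Direction.** The documents show the mini-app leading to a study hospital and the control materials naming local referral in addition to a study-hospital route. This makes c(O2O-PEP) > c(control) the more plausible ordering. No figure in the article establishes it.

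**The case against.** A fair defence has six parts.

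- **Controls are not sent away from the study hospitals.** The control section gives them a standard route there, so only part of their initiations could be missed. That the local services are different providers is an inference, drawn from their separate listing and from there being other designated hospitals. This stands, and it limits the size.
- **Intervention participants may also start PEP elsewhere.** Nothing in the article prevents it, and the 72-hour window could encourage it. This stands, and it is why the direction is likely and not shown.
- **Geography.** The eligibility criterion that participants "are going to reside in Jiangsu province and Qingdao city in the following 6 months after recruitment", set against a single study hospital in Jiangsu, might suggest selective loss among controls. It does not by itself: distance affects both arms alike. It supports under-counting overall, not a difference between arms.
- **The survey may already feed the outcome.** Table 1 and the follow-up surveys collect PEP uptake in both arms, and a fuller protocol might say how the sources are combined. But the article does name a source and a coding rule, and that rule does not use the survey. The passages need reconciling.
- **Hospital records are objective.** Participants know which service they received, and the Randomization section describes blinding only to the allocation sequence. Self-report could bring its own arm-dependent error. This stands as a cost of the change, but it does not justify scoring known initiations as 0.
- **This is a 50-person pilot.** Its risk ratio will be very imprecise under any definition, and the Discussion acknowledges the small sample. This stands, and it places most of the value of a fix in the main trial.

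**Conclusion.** The outcome rule as written scores PEP started outside the study hospitals as no PEP, and it does not match the article's own analysis wording or its planning rate. The routes to PEP differ by arm in a way that is likely to lose more control initiations and so inflate the risk ratio for O2O-PEP.

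A reader might go further and conclude that bias in favour of the intervention is established, or that a null effect would appear as a risk ratio of 1.4 to 1.9. The documents do not support either. Those values need assumed control capture of 50% to 70% against 95% in the intervention arm. At 90% the value is 1.06, and at equal capture it is 1.00. The direction rests on the described routes, and the size rests wholly on assumed shares.

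The point is worth acting on because it concerns the primary efficacy outcome and the repair is cheap.

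**What to change.** Reconcile the outcome definition with the Follow-ups section, Table 1 and the analysis section:

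1. Define the primary efficacy outcome as any PEP initiation dated after randomization, at any provider.
2. Ascertain it identically in both arms, from study-hospital records or from the PEP-uptake item in the 1-, 3- and 6-month surveys.
3. Add date and place of initiation to that item, with documentation from the participant where available.
4. Report the hospital-record-only definition as a sensitivity analysis, side by side with the primary result.
5. Tabulate place of initiation by arm. This would give the main trial the capture shares that are now unknown.

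**Cost.** Revised outcome wording and a few survey fields, settled before data collection because date and place may be hard to recover later. Some events will rest on unblinded self-report, and survey response may differ by arm. The plan must therefore also say how a participant with no hospital record and no survey answer is handled. Reporting both versions lets the reader see how far the result depends on the source.
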